### 2.2. Population

In Phase A, a pragmatic approach will be used, tracking each target population group according to individual governments’ distributional plans, which in most countries went from HCWs, to SAs, to TAs, to MIs. The sample of Phases B and C will be pre-identified based on the outcomes of Phase A.

If more than 368 of the Phase A participants show their interest in joining Phase B, no additional recruitment will be required. If less than 368 of the Phase A participants show their interest in participating in Phase B, additional recruitment will be carried out, targeting HCWs who will receive booster doses. In case of the emergence of special side effects after booster doses, additional recruitment of a sample of HCWs will be required.

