#### 2.2.3. Sample Size

The pragmatic sample size for each target group in each country will be calculated using Epi Info ^TM^ version 7.2.4 (CDC, Atlanta, GA, USA. 2020). The formula of population survey studies will be used to achieve a 5% margin of error and a 95–99% confidence level [29]. The expected frequency (outcome probability) is assumed to be 60%, as the prevalence of side effects following COVID-19 vaccines ranged between 62% and 93% in our previous studies [21,22] (Figure 1).

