## Figures and Tables

**Figure 1 ijerph-18-07859-f001:**
[figure not shown]
Sample size of healthcare workers (HCWs) in the Czech Republic—Epi-Info ^TM^ version 7.2.4. Population size: Total number of healthcare workers in the Czech Republic in 2017 [30]. Expected frequency: The overall prevalence of side effects following COVID-19 vaccines ranged between 62% and 93%; therefore, 60% was assumed as a threshold. Acceptable margin of error: The permissible level for all CoVaST groups will be 5%. Design effect: One—per the recommendation of the CDC for simple sampling [29]. Clusters: One—per the recommendation of the CDC for simple sampling [29]. The pragmatic sample size is 368–635 (CI 95%–99%).

**Table 1 ijerph-18-07859-t001:** The projected timeline of the COVID-19 vaccines safety tracking (CoVaST) study.

Phase	Stage	Population	Schedule
Phase A	Stage A.1.	HCWs	May–August 2021
	Stage A.2.	SAs	June–December 2021
	Stage A.3.	TAs	June–December 2021
	Stage A.4.	MIs	June–December 2021
Phase B	Stage B.1.	HCWs	October 2021–February 2021
	Stage B.2.	SAs	November 2021–April 2022
	Stage B.3.	TAs	November 2021–April 2022
	Stage B.4.	MIs	November 2021–April 2022
Stage C	Stage C.1.	HCWs, SAs, TAs, MIs	January–December 2022
	Stage C.2.	HCWs, SAs, TAs, MIs	January–December 2023
	Stage C.3.	HCWs, SAs, TAs, MIs	January–December 2024
	Stage C.4.	HCWs, SAs, TAs, MIs	January–December 2025
	Stage C.5.	HCWs, SAs, TAs, MIs	January–December 2026

HCWs = Healthcare Workers; SAs = Senior Adults; TAs = Teachers and Academics; MIs = Minors.

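### The Phase B recruitment trigger reuses a one-group, one-country respondent count as a pooled count of interest with HCW-only top-up, so it does not ensure the 5% margin for each target group

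*Protocol article*

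**What the plan says.** Section 2.2 (Population) gives the Phase B rule: "If more than 368 of the Phase A participants show their interest in joining Phase B, no additional recruitment will be required". If fewer show interest, "additional recruitment will be carried out, targeting HCWs who will receive booster doses". A second top-up route is also confined to HCWs: "In case of the emergence of special side effects after booster doses, additional recruitment of a sample of HCWs will be required". None of these sentences names a target group or country for the count of 368, and none requires that an interested person has been boosted or has returned a questionnaire.

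Other parts of the article set the standard that the rule should serve:

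- Section 2.2.3 (Sample Size): "The pragmatic sample size for each target group in each country will be calculated" in Epi Info, "to achieve a 5% margin of error and a 95–99% confidence level", with an expected frequency of 60%.
- Figure 1 caption: 368 (95%) to 635 (99%) is the result for HCWs in the Czech Republic, with design effect one. The caption gives 5% as the permissible margin for every CoVaST group.
- Table 1: Phase B has four stages, one each for HCWs, senior adults (SAs), teachers and academics (TAs) and minors (MIs).
- Section 3: Phase B results are to be published internationally for each target group.
- Section 2.1.2: Phase B studies short-term side effects after booster doses.

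**The concern.** The number 368 changes meaning between Figure 1 and Section 2.2. In Figure 1 it is a count of respondents in one group in one country. In Section 2.2 it is a count of people who say they are interested, taken over Phase A participants without distinction of group or country. Three consequences follow.

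1. **Unit.** Only people who receive a booster and answer contribute to a Phase B estimate. The article recognises this for the top-up, which targets HCWs due to be boosted, but not for the count that decides whether a top-up is needed.
2. **Scope.** Sizing and reporting are by group, but the trigger is pooled. It can be met while one or more groups are small.
3. **Remedy.** A shortfall is filled with HCWs whichever group is short. More HCWs add nothing to the precision of the SA, TA or MI estimate.

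At stake is whether the group-specific booster estimates promised in Section 3 reach the precision that the article states for all groups. A group left nearly empty when recruitment closes cannot be repaired in the analysis.

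**Working it through.** **Inputs from the article.** p = 0.60, d = 0.05, 95% and 99% confidence (Section 2.2.3); design effect 1 (Figure 1 caption); four Phase B groups (Table 1); trigger of more than 368, so 369 (Section 2.2).

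**Inputs assumed.** Booster uptake of 30–90% and response among the boosted of 40–80%; the article gives neither. The Czech HCW population size is in the figure that is not shown, so 200,000–250,000 was tried.

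**Step 1: reproduce 368–635.** n₀ = z²p(1−p)/d².

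- 95%: 1.96² × 0.24 / 0.0025 = 368.8.
- 99%: 2.576² × 0.24 / 0.0025 ≈ 637.0.
- With the finite population correction, n = N·p(1−p) / [(d²/z²)(N−1) + p(1−p)], the results for N = 200,000–250,000 are 368.1–368.2 and 634.9–635.3.

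Both stated figures reproduce. The arithmetic behind 368 is sound; the problem lies in its reuse.

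**Step 2: precision by group at the trigger, with no loss.** Half-width = 1.96 × √(0.24/n).

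| Split of 369 (HCW/SA/TA/MI) | HCWs | Each other group |
|---|---|---|
| All HCWs | 369, ±5.0 | none |
| 25/25/25/25% | 92, ±10.0 | 92, ±10.0 |
| 70/10/10/10% | 258, ±6.0 | 37, ±15.8 |

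The equal split needs no assumption about uptake or response: 1.96 × √(0.24/92) = 0.100. At the threshold, only the case in which everyone belongs to one group gives ±5.0.

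**Step 3: from interest to boosted respondents, groups pooled.** Yield = 369 × uptake × response. The last column is 368/(uptake × response), the expressions of interest needed for 368 respondents in one group.

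| Uptake × response (assumed) | Respondents from 369 | Half-width | Interest needed per group |
|---|---|---|---|
| 90% × 80% | 266 | ±5.9 | 512 |
| 50% × 60% | 111 | ±9.1 | 1,227 |
| 30% × 40% | 44 | ±14.4 | 3,067 |

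**Step 4: compare the trigger with the article's own sizing.** Four groups at 368 each make 4 × 368 = 1,472 respondents in one country at 95%. A Phase A of that size would meet the pooled trigger once 369/1,472 = 25% expressed interest. If interest were even across groups, that is the 92-per-group case of Step 2.

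**The case against.** **It is a floor, not a cap.** A reader might infer that Phase B stops at 368, or cannot reach ±5 points in any group. The text does not support that. Sections 2.1.2 and 2.4.2 send the questionnaire to Phase A volunteers who expressed interest, with no upper limit, so the realised sample may be much larger. This stands. The rule fails to ensure ±5 points; it does not prevent it. The figures above describe the situation near the threshold, and the size of any real shortfall depends on uptake, response and group mix.

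**It may have been meant for HCWs, or per country.** Since 368 is the Czech HCW figure, an HCW-only reading is plausible and would make an HCW top-up coherent. Section 2.2 does not say so, however, and the other three Phase B groups would then have no rule. A per-country reading still pools the groups, still counts interest and still tops up with HCWs.

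**Preferring HCWs has a stated reason.** The Strengths and Limitations section says that HCWs are recruited to limit reporting bias. That is a reason to include them, but it does not make them substitutes for seniors, teachers or minors in estimates reported by group.

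**Phase B is descriptive and the article is condensed.** A small group would show as a wider interval, and invitation numbers can be left to a fuller document. This lowers the severity. It does not remove the conflict, because the rule is explicit and is at odds with Sections 2.2.3 and 3.

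**A tempting further charge.** A reader might infer that enlarging the HCW sample when special side effects emerge inflates their estimated frequency. The article neither defines such effects nor says that the extra HCWs will be pooled. Pooling a fresh independent sample would pull a high triggering rate back towards the truth, not raise it. Recruiting more people to follow up a safety signal is not in itself a fault, and no such charge is made here.

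**Conclusion.** The point holds as a mismatch between the Phase B trigger and the article's own sizing and reporting by group. The rule allows recruitment to close with about 92 people per group (±10.0 points, twice the stated margin) under an equal split and no loss at all. With loss, the pooled yield from 369 expressions of interest ranges from about 266 (±5.9) to 44 (±14.4) over the assumed rates. An HCW-only top-up cannot correct a shortfall in the other three groups.

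The equal-split figure rests on the article's 60% frequency, its design effect of one and a total close to the threshold. The yield figures also rest on uptake and response rates that the article does not give. The conclusion is that the stated margin is not secured, not that it will necessarily be missed.

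**What to change.** Revise Section 2.2 before Phase B recruitment closes:

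- State the scope of the trigger. Count completed post-booster questionnaires, separately for each target group (and for each country where national results will be published), against the Section 2.2.3 figure.
- Direct any top-up to the group that is short.
- Where that is not feasible, restate the achieved margin for that group in place of 5%.
- If 368 was meant for HCWs only, say so, and give the rule or the expected margin for SAs, TAs and MIs.
- Cover the case of exactly 368, which the present wording leaves open.

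The cost is a change of wording, a running count by group and more invitations, mainly to existing Phase A contacts. Meeting the 95% figure in all four groups means at least 1,472 completed questionnaires (per country, if the scope of Section 2.2.3 is kept). Where a group cannot reach its number, the cost is a wider margin, openly reported.

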### Objectives

This project aims to actively monitor the side effects and effectiveness of COVID-19 vaccines worldwide. The primary objectives of the project include:(a)To estimate the prevalence of both local and systemic side effects following each of the COVID-19 vaccines among healthcare workers (HCWs), teachers and academics (TAs), senior adults ≥65 years old (SAs), and minors ≤18 years old (MIs);(b)To evaluate the potential demographic and medical risk factors for the frequency and intensity of side effects;(c)To evaluate the long-term safety of COVID-19 vaccines.

The secondary objectives include:(a)To evaluate the relative effectiveness and safety of COVID-19 vaccines in relation to one another;(b)To evaluate the impact of palliative medications used by the vaccinated individuals for short-term side effect resolution.

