#### 2.1.2. Phase B

A validated, self-administered questionnaire will be developed and delivered online to the volunteers who participated in Phase A and expressed their interest in reporting on their long-term outcomes. The short-term side effects following booster doses will be investigated in this phase. This phase is tentatively planned to take place from October 2021 until April 2022.

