## 3. Registration and Dissemination

The study protocol has been registered with the US National Library of Medicine registry (ClinicalTrials.gov, accessed on 9 May 2021), with the identifier NCT04834869 [33]. The ClinicalTrials.gov (accessed on 9 May 2021) record will be regularly updated by the project’s principal investigators, and any deviations from the protocol will be mentioned and justified a priori in the electronic record, and in the manuscript of the final study.

The investigators aim to disseminate the results of the project in peer-reviewed journals on a regular basis. For the results of phase A, the international data for each target group will be published once the data collection is completed. Meanwhile, national data of each participating center will be published as interim results. For the results of phase B, the international data for each target group will be published once the data collection is completed. For the results of phase C, the international data for all target groups will be published on an annual basis once the data collection is completed.

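### Signal-triggered recruitment in Phase B names only healthcare workers, so a signal in minors, senior adults or teachers would bring in essentially nobody from the affected group

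*Protocol article*

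**What the plan says.** The protocol article, section 2.1.2 (Phase B), gives the purpose: "The short-term side effects following booster doses will be investigated in this phase". Primary objective (a), under Objectives, is "To estimate the prevalence of both local and systemic side effects following each of the COVID-19 vaccines", in healthcare workers (HCWs) and also in "teachers and academics (TAs), senior adults ≥65 years old (SAs), and minors ≤18 years old (MIs").

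Table 1 gives each of these groups its own Phase B stage: B.1 for HCWs, B.2 for SAs, B.3 for TAs and B.4 for MIs. Section 3 adds: "For the results of phase B, the international data for each target group will be published once the data collection is completed".

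Section 2.2 (Population) has two rules for extra recruitment into Phase B.

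- **By numbers.** "If more than 368 of the Phase A participants show their interest in joining Phase B, no additional recruitment will be required". If fewer come forward, "additional recruitment will be carried out, targeting HCWs who will receive booster doses".
- **By signal.** "In case of the emergence of special side effects after booster doses, additional recruitment of a sample of HCWs will be required".

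The signal rule does not require that the side effect arose in HCWs, and it names no other group. It does not say how the added sample is to be analysed.

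**The concern.** The signal rule fixes who is recruited before anyone knows where the signal will be. If the side effect emerges in HCWs, the rule fits. If it emerges in minors, senior adults or teachers, the study must recruit more people, but from a group that is not affected.

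Two things are at stake. First, the affected group gains no information when it is most needed. Second, the new data will exist and will concern the side effect in question, so a low or zero count among HCWs may be taken as an answer for the other group. The study offers its findings to support public confidence in vaccines, so that misreading would matter.

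A lesser issue depends on the analysis. Outcomes are self-reported, and people who join after a side effect has become known may report it more readily. If they were merged with the earlier HCW cohort, the HCW estimate could be biased.

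**Working it through.** **1. Where 368 comes from.** Section 2.2.3 states: "The formula of population survey studies will be used to achieve a 5% margin of error and a 95–99% confidence level". The expected frequency is 60% and the design effect is 1 (Figure 1 legend). For a large population, n = z² × p(1 − p) / d².

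- 95%: 1.960² × 0.24 / 0.0025 = 368.8.
- 99%: 2.576² × 0.24 / 0.0025 = 637.0.

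The population size is in a figure that is not shown. With a finite population correction and an assumed population of 200,000 to 300,000, the results are 368.1–368.3 and 634.9–635.6. The stated 368–635 is reproduced. It is the size for one group (HCWs) in one country. I use 368 below only as a convenient number, because section 2.2 uses it as the Phase B threshold.

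**2. Groups covered against group recruited.**

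| Group | Phase B stage | Results promised | Added after a signal |
|---|---|---|---|
| HCWs | B.1 | yes | yes |
| SAs | B.2 | yes | none named |
| TAs | B.3 | yes | none named |
| MIs | B.4 | yes | none named |

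An HCW sample contains essentially no minors. Any HCW who is 65 or over, or who also teaches, would be there by accident; the article gives no figures for such overlap.

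**3. What the rule does for the affected group.** Assumptions: 368 respondents split equally (368 / 4 = 92 per group), a 2% rate in one non-HCW group, and 368 people added. The standard error is √[p(1 − p) / n].

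- Before any addition: √(0.02 × 0.98 / 92) = 1.46 percentage points.
- After adding 368 HCWs: the affected group still has 92, so 1.46 points.
- If the 368 came from the affected group, n = 92 + 368 = 460: √(0.02 × 0.98 / 460) = 0.65 points.

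After the HCW addition, HCWs make up (92 + 368) / 736 = 62.5% of respondents.

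For a null result, zero cases among 368 added HCWs gives an approximate upper 95% limit of 3 / 368 = 0.8% for HCWs. It sets no limit for minors or seniors.

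**4. The pooling question.** This is a simulation with assumed inputs. X ~ Bin(368, r) cases arise in the original cohort. If X ≥ k, 368 HCWs are added who report at m times the true rate r, and the estimate is the total number of cases divided by 736. Otherwise it is X / 368. The last three columns give the mean estimate divided by the true rate.

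| r | k | Trigger fires | m = 1 | m = 2 | m = 3 |
|---|---|---|---|---|---|
| 0.1% | 1 | 31% | 0.66 | 0.81 | 0.96 |
| 0.1% | 3 | 0.6% | 0.98 | 0.98 | 0.98 |
| 0.5% | 1 | 84% | 0.92 | 1.34 | 1.76 |
| 0.5% | 3 | 28% | 0.87 | 1.01 | 1.15 |
| 1% | 1 | 98% | 0.99 | 1.47 | 1.96 |
| 1% | 3 | 71% | 0.92 | 1.27 | 1.63 |

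The ratio runs from 0.66 to 1.96, so the bias can go either way.

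Among studies in which the trigger fired, the pooled mean exceeds the truth even at m = 1. That comes from selecting studies that saw cases, not from the added HCWs. At r = 0.5% and k = 1, the original cohort alone has ratio 1 / 0.842 = 1.19, and pooling brings it to (1.19 + 1) / 2 = 1.09.

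**The case against.** **HCWs may be the right group.** Table 1 starts Phase B with HCWs in October 2021 and the other groups in November, so an early signal could well appear in HCWs first. The Strengths and Limitations section also gives a reason to recruit HCWs: their health literacy should limit reporting bias. The rule does not forbid recruiting others. All of this is fair, and it makes the mismatch conditional on where the signal arises. It does not remove the mismatch, because better reporting by HCWs says nothing about risk in minors or seniors, and the only recruitment the rule requires is of HCWs.

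**Separate reporting limits the damage.** Results are promised per target group, so added HCWs could alter only the HCW estimate. That stands, and I make no claim about a prevalence pooled over groups.

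**The stronger reading.** A reader might infer that Phase B enrolment depends on its own outcome, and that the reported rate of the triggering side effect would therefore be inflated by some multiple. The documents do not support this. They never say that the added sample is merged with the cohort, and its analysis may be set out in a full protocol or analysis plan that is not shown. The signal might come from outside the study. Snowballing, which could draw in people who had the effect, is described for Phase A only. Any fold-change would restate whatever reporting rate was assumed for the new recruits, and the table shows ratios below 1 as well as above.

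**Conclusion.** The concern holds in a limited form. Section 2.2 names HCWs alone for signal-triggered recruitment, while Phase B covers and reports four groups. For a signal outside HCWs, the number of respondents added by design from the affected group is essentially zero. Under the stated assumptions (92 per group, a 2% rate, 368 added), the standard error in that group stays at 1.46 percentage points instead of falling to 0.65. Other group sizes and rates would change these figures, but not the fact that adding HCWs leaves the affected group's precision where it was.

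Bias from pooling is only a possibility. It depends on whether the samples are merged, what triggers recruitment, how many are added and how they report. I claim no size or direction for it. It justifies keeping the two samples identifiable, and no more than that.

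**What to change.** In section 2.2, change the signal sentence so that the extra sample is drawn from the target group or groups in which the side effect emerged, using that group's Phase A recruitment channel in section 2.4.1. Add that these participants are flagged by enrolment date and reported separately from the Phase B prevalence estimate.

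The cost is a sentence or two and one data field. Recruiting minors or seniors may be slower than recruiting HCWs. The triggered sample would add no precision to the main Phase B estimate. The Phase A channels for HCWs, seniors and teachers include snowballing, so following them after a signal is known brings some risk of self-selection, which is a further reason for reporting that sample on its own.

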#### 2.2.1. Inclusion Criteria

HCWs, TAs, SAs, and MIs who received a COVID-19 vaccine in the post-authorization phase;The recently vaccinated individuals who received their vaccine dose within the previous 30 days will be prioritized to be invited for the study, even though the study will not be limited to the recently vaccinated individuals;Participating subjects should be at least 18 years old in order to give their informed consent independently, or in case of the minors (below 18 years old), their caregivers will be asked to give their informed consent.

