#### 2.1.1. Phase A

A validated, self-administered questionnaire will be developed and delivered online to the target population groups (HCWs, TAs, SAs, and MIs). In certain circumstances, telephone interviews and paper questionnaires will be used instead of the online questionnaire in order to adapt to the local setting. The questionnaire will inquire about the short-term side effects following either the first dose, the second dose, or both doses of the COVID-19 vaccine. The side effects will be classified as local or systemic, and their onset, duration, and intensity will be self-assessed and self-reported by the participating subjects. This phase is planned to take place until 31 December 2021.

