### Strengths and Limitations

To the best of the authors’ knowledge, this is the first multinational study aiming to monitor the safety of various COVID-19 vaccines, especially following booster doses. Another strong point of this study is its unified evaluation instrument, target groups, and methods, which will be used in all participating countries, and should maximize the results’ internal validity. Recruiting HCWs is intended to limit the reporting bias that is naturally predicted in this survey-based study, due to the fact that HCWs retain high levels of health literacy and scientific interest. This study is one of the early-registered studies that are concerned with the long-term safety of COVID-19 vaccines, and their effectiveness.

In general, this study is limited by the heterogeneous time span between vaccination and survey commencement across the participating countries; therefore, subgroup analysis according to the time span will be carried out during data analysis. One more limitation is recall bias, as in various countries, vaccination covered the majority of population who intended to be vaccinated. Due to the recruitment of participants who received the vaccine in the first half of 2021, there is a possibility of recall bias when filling out the questionnaire. Since COVID vaccination is a hot topic worldwide, we assume that participants could remember all experienced side effects well.

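### Phase A sets no limits on time since dose and assumes full recall, so prevalence pooled over all intervals, and contrasts between groups or vaccines, can carry recall bias that an unspecified subgroup analysis will not remove

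*Protocol article*

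**What the plan says.** - **Eligibility (2.2.1, Inclusion Criteria).** People dosed in the last 30 days are to be invited first, but the same criterion then opens Phase A to everyone else: "even though the study will not be limited to the recently vaccinated individuals". The 30 days govern who is invited first. They do not govern who is eligible or who is analysed, and no minimum interval is given.
- **Survey period (2.1.1, Phase A; Table 1).** "This phase is planned to take place until 31 December 2021". Table 1 closes the healthcare-worker stage in August 2021 and the senior, teacher and minor stages in December 2021.
- **Limitations (Strengths and Limitations).** "Due to the recruitment of participants who received the vaccine in the first half of 2021, there is a possibility of recall bias". The next sentence reads: "Since COVID vaccination is a hot topic worldwide, we assume that participants could remember all experienced side effects well". For the uneven gap between vaccination and survey start across countries, the remedy is that "subgroup analysis according to the time span will be carried out during data analysis". No cut points are given.
- **Objective affected (Objectives).** Primary objective (a) is "To estimate the prevalence of both local and systemic side effects following each of the COVID-19 vaccines".
- **Analysis (2.7).** Frequencies and percentages, then association tests for risk factors. No time window is mentioned.
- **Data available (2.3).** The questionnaire records the date of each vaccine dose.

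**The concern.** Short-lived symptoms, with their onset, duration and intensity, are self-reported at whatever interval the respondent happens to answer. Someone answering after many months may have forgotten mild symptoms. Someone answering the day after a dose may not yet have had them. Both errors push the measured prevalence of any side effect downwards.

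Giving recent vaccinees priority concedes that recency matters, and the recall assumption then takes the concession back. The subgroup analysis can reveal a trend with time. It does not take the bias out of a figure pooled over all intervals, or out of a risk-factor or between-vaccine comparison that ignores time since dose. As worded, it also concerns the gap between vaccination and survey start across countries, which is not clearly each respondent's own interval from dose to answer.

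The comparisons are exposed because time since dose may differ by target group, country and vaccine. Section 2.2 describes a rollout that reached the groups in sequence, while Table 1 gives three of the four groups the same June–December survey window. Neither of the protocol's other safeguards tests recall over months. The test–retest exercise in 2.3 (at least 10 volunteers, at least two weeks apart) measures repeatability. The health-literacy argument in Strengths and Limitations covers healthcare workers, but not seniors or parents answering for children.

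**Working it through.** **1. The protocol's own figure.** Inputs from 2.2.3 and the Figure 1 legend: p = 0.60, d = 0.05, design effect 1. With n0 = z²p(1−p)/d²:
- 95%: 1.96² × 0.24 / 0.0025 = 368.8
- 99%: 2.576² × 0.24 / 0.0025 = 637.0

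The population size is in a figure not shown. With an assumed N = 250,000, n0/(1 + (n0−1)/N) gives 368.2 and 635.3. The stated 368–635 is reproduced. The 5-point margin covers sampling error only.

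**2. Longest recall interval.** Take 1 January 2021 as the earliest dose within the first half of 2021.
- Healthcare workers, to 31 August 2021: 242 days, about 8 months.
- Seniors, teachers and minors, to 31 December 2021: 364 days, about a year.
- Lower end, all groups: 0–1 day, since no minimum is set.

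**3. Effect of forgetting on a pooled prevalence.** Bias = −p × f × (1−s), where f is the share of respondents beyond 30 days and s is the share of their true cases still reported. The documents give neither f nor s, so both are assumptions. At p = 0.60:

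| f | 10% forgotten | 20% forgotten |
|---|---|---|
| 25% | −1.5 points | −3.0 points |
| 50% | −3.0 points | −6.0 points |
| 75% | −4.5 points | −9.0 points |

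The bias passes 5 points when f(1−s) exceeds 0.05/0.60 = 8.3%. With half the sample beyond 30 days, that means more than about 17% of their cases forgotten.

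**4. Effect on interval coverage.** At n = 368 the standard error is √(0.24/368) = 0.0255. A 3-point bias is 0.03/0.0255 = 1.17 standard errors. Coverage of a nominal 95% interval is then Φ(1.96 − 1.17) − Φ(−1.96 − 1.17), about 78%. A 5-point bias gives about 50%.

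**5. Very early respondents.** Assume that 10% of respondents answer early, when 50–90% of their eventual cases have appeared. The bias is 0.60 × 0.10 × 0.50 = 3.0 points down to 0.60 × 0.10 × 0.10 = 0.6 points, again downwards.

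**6. Precision of the band up to 30 days.** The share of respondents in it is not given. Half-width = 1.96 × √(0.24/n):

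| Share of 368 in band | n | Half-width | Recruits needed for 368 in band |
|---|---|---|---|
| 25% | 92 | 10.0 points | 1,472 |
| 50% | 184 | 7.1 points | 736 |
| 75% | 276 | 5.8 points | 491 |

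**The case against.** The protocol is not blind to the problem. It invites recent vaccinees first, has recruitment follow each government's rollout, collects dose dates, lists both time span and recall as limitations, and promises an analysis by time span. Recruiting along the rollout tends to equalise intervals between groups, and how much imbalance remains is unknown. All of this stands and limits the size of the problem. None of it fixes an analysis that removes the bias.

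Several stronger readings are tempting, and the documents do not support them:
- **That the headline prevalence will be the pooled figure.** Section 2.7 names no lead analysis set, and an analysis plan may exist that is not shown. What can be said concerns any pooled figure.
- **That the bias is known to match the 5-point margin.** The forgetting rates and the share beyond 30 days have no source in the documents.
- **That answers within a week of the dose are censored.** A symptom that has already resolved has a complete duration. Only symptoms still present at response are censored.
- **That the main analysis should be confined to, say, 7–30 days after the dose.** Only 30 days appears in the protocol. A mandatory restriction would forfeit the 5% margin in many settings. It would also drop first-dose reports from people whose first dose is more than 30 days old, tilting first-dose estimates towards people with only one dose so far.

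The recall sentence is commentary, so removing it alone would change no analysis.

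**Conclusion.** The point holds as a design and analysis weakness that should be corrected. The protocol states an eligibility rule open at both ends and a full-recall assumption, and the remedy it offers has no cut points. Prevalence pooled over all intervals, and unadjusted contrasts between groups or vaccines, can be biased by time since dose.

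On the illustrative inputs (60% prevalence, half of respondents beyond 30 days, 10–20% of their cases forgotten), the shortfall is 3–6 points. At n = 368, the 3-point case alone reduces 95% coverage to about 78%. The illustration treats recall error purely as forgetting; symptoms wrongly attributed to the vaccine would act the other way. The size is therefore conditional. The lack of a fixed way of handling time since dose is not.

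**What to change.** In section 2.7, using the dose dates already collected:
1. Compute each respondent's interval from dose to response, separately for each dose.
2. Report prevalence in pre-specified bands of time since dose. Lead with the band up to 30 days, which is the protocol's own window, state its actual interval width, and show the full sample alongside.
3. Include time since dose as a covariate in all risk-factor and between-vaccine models.
4. Treat symptoms unresolved at response as censored for duration, and add a sensitivity analysis without very early respondents.
5. Do not rely on the full-recall assumption in Strengths and Limitations.

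**Cost.** No new data items are needed, but the lead band will be smaller than 368–635. With 184 respondents the half-width is about 7.1 points. Claim the 5% margin only for bands that reach the target; holding 368 in the lead band when half of respondents qualify takes 736 recruits. Read first-dose results in the recent band together with the full-sample results, because that band over-represents people with only one dose so far.
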